A semistructured questionnaire will be used to assess the economic data related to the health services use. In addition, the use of medications, history of medical consultation and/or emergency care, history of hospitalizations related to urinary problems, and surgical procedures will be verified and will be followed up for 6 months. The cost of which treatment for each participant will be assessed according to the use of health services and calculated by the price list of the Brazil’s Unified Health System and according to the physiotherapist’s fees established by the Federal Council of Physiotherapy and Occupational Therapy and also by average of three budgets for private treatment. Costs will be computed with the use of sanitary napkins, diapers and liners, medications, exams related to urinary problems, consultation with health professionals (such as nurses, doctors and/or physiotherapists), and other interventions and surgical procedures.

In order to compose the economic evaluation, the expenses related to materials used during physical evaluations and intervention (such as gloves, condoms, lubricants, disposable sheets, pressure gauge, NMES devices and probes, and the physiotherapist assessment price) will be computed. In addition, to compose the health costs of tertiary care, information related to hospitalization history, surgery history, average hospitalization time, and absenteeism for health reasons will be verified. To convert the procedures into current currency, the values informed by the Brazil’s Unified Health System price tables and/or based on the market average price will be used. Monetary data will be made in the national currency (real) and converted into international currency with an updated conversion rate.

To compose the indirect costs, the participants will be asked about the days of absence from work (paid or unpaid), which will be computed by means of specific price weights for the female gender and transportation to get to the place where the treatment will be carried out. In addition, the distance between the participants home to the location where the treatment will be applied will be computed. Therefore, the price of the means of transport for those using public transport or weighting of the price of the fuel of private transport will be assessed.

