### Statistical analysis plan

The statistical analysis will be performed by a researcher without involvement in the evaluations and treatment intervention. The software SPSS 16.0 and R 3.5.1 will be used for the analysis of data. The level of significance will be set at 5%. The normality of the residues will be verified by the Shapiro-Wilk test.

The comparison of SUI, voiding habits, and quality of life between groups CG, IG 1, and IG 2 and between stages (pre-treatment, re-assessment after finished the intervention protocol and follow-up), as well as the interactions between groups, will be performed by means of analysis of variance (ANOVA) of mixed models considering group and time factors for repeated measures, if the residuals present normality with post hoc contrasts (group IG1 and IG2 versus group CG, and group IG1 versus group IG2).

The first statistical procedure will verify, in general and at each evaluation stage (pre-treatment, re-assessment after finished the intervention protocol and follow-up), if SUI urine loss per day related to stress (e.g., coughing, sneezing, physical exercise or household activities) and quality of life differ into the three groups. The null hypothesis is that all groups will present equal results during outcomes assessments. The alternative hypothesis is that IG 1 will differ from CG and that IG2 will differ from the CG as well.

The second statistical procedure aims to verify if there is alteration in the SUI, urine loss per day related to stress (e.g., coughing, sneezing, physical exercise or household activities), and quality of life throughout the four stages of study evaluation (pre-treatment, re-assessment after finished the intervention protocol and, follow-up of the 3rd and 6th month) within each of the groups. The null hypothesis is that the behavior is the same throughout the stages in each group. The alternative hypothesis is that there is a difference in the stages in each group.

The quantitative variables will be presented as minimum value, maximum value, mean, median, and standard deviation. Categorical variables will be presented as frequencies and percentages.

Details of the statistical analyzes are as follows:

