At the interview and physical assessment, the subjective interview record will be applied, which generates qualitative variables that will be presented as frequencies and percentages and quantitative variables that will be presented as minimum value, maximum value, mean, median, and standard deviation. One researcher will perform the vaginal palpation and the manometry assessment, as well as applied SF6-D, KHQ, King´s Health Questionnaire for Scoring Algorithm, health cost analysis form, and 24 h-voiding diary, which will result in quantitative scales that will be presented as minimum value, maximum value, mean, median, and standard deviation.At the end of treatment sessions, vaginal palpation and manometry will be repeated, as well as SF6-D, KHQ, King’s Health Questionnaire for Scoring Algorithm, health cost analysis form, and the 24 h-voiding diary, which will result in quantitative scales that will be presented as minimum value, maximum value, mean, median, and standard deviation.At the 1st to the 6th month of follow-up, the health cost analysis form will be applied, and at the 3rd and 6th month of follow-up, the SF6-D, KHQ, King´s Health Questionnaire for Scoring Algorithm, and health cost analysis form will be completed, which will result in quantitative scales that will be presented as minimum value, maximum value, mean, median, and standard deviation.At the end of the treatment, the ANOVA for repeated measurements will be applied to verify the effects of the three groups and the two stages (pre-treatment and re-assessment after finished the intervention protocol) and the interactions between them according the results related to the vaginal palpation, manometry, SF6-D, KHQ, King´s Health Questionnaire for Scoring Algorithm, health cost analysis form, and 24 h-voiding diary, if the residues present normality. If the residues do not present normality, a non-parametric test will be applied.At the end of the follow-up, the repeated measures ANOVA will be applied to verify the effects of the three groups and the eight stages (pre-treatment, re-assessment after finished the intervention protocol and 1, 2, 3, 4, 5, and 6 months of the follow-up) and the interactions between them considering the SF6-D, KHQ, King’s Health Questionnaire for Scoring Algorithm, health cost analysis form, and 24 h-VD, if the residues present normality. If the residues do not present normality, a non-parametric test will be applied.The cost-utility assessment will be performed by the quality-adjusted life years (QALY), which combines the length and quality of life into a single index number between 0 and 1, where 0 corresponds to a health state judged to be equivalent to death and 1 corresponds to optimal health [35, 36]. To conduct the statistical analysis, the mean between-group cost differences will be corrected for their baseline, and the total costs will be divided by the costs differences for incremental analysis of cost-effectiveness and cost-utility ratios. Subsequently, a deterministic cost-utility value and a probabilistic one will be determined by applying a bootstrapping technique of 5000 interactions and the bias-corrected, in order to compare health costs between groups. The results will be presented with the confidence interval of 95% (95% CI). The likelihood of the cost-effective intervention will be estimated by the cost-effectiveness acceptability curves to compared values other than willingness to pay [37]. The Kaplan-Meier method and the Log-Rank between-group comparison test will be applied in order to assess the sensitivity of the uncertainty of each parameter by assessing the changes in the results in the range of parameter values [38].

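### Health cost is compared between arms in two ways with different null hypotheses, and the protocol does not say which one carries the inference

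*Protocol article*

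**What the plan says.** Health cost analysis is a named secondary outcome (Protocol article, Measurement of results, primary and secondary outcomes). The Statistical analysis plan then handles it in two places.

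- **ANOVA rule.** The cost form is among the variables analysed by repeated-measures ANOVA for group, stage and their interaction, at the end of treatment (two stages) and at the end of follow-up (eight stages). The follow-up item reads "health cost analysis form, and 24 h-VD, if the residues present normality. If the residues do not present normality, a non-parametric test will be applied". The end-of-treatment item ends with the same switch. The trigger is stated earlier in the section: "The normality of the residues will be verified by the Shapiro-Wilk test". The fallback test is not named.
- **Cost-utility item.** Here "the mean between-group cost differences will be corrected for their baseline", and a bias-corrected bootstrap with 5000 resamples is applied "in order to compare health costs between groups", with 95% confidence intervals and acceptability curves.

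On content, Evaluation tools says: "Costs will be computed with the use of sanitary napkins, diapers and liners, medications, exams related to urinary problems". The list goes on to consultations, other interventions and surgical procedures, and adds hospitalisation and absenteeism.

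**The concern.** An economic comparison concerns arithmetic mean cost, because the mean times the number of women treated gives the budget. The bootstrap item addresses that quantity. A rank test does not: its null is that neither arm's costs tend to exceed the other's. Two arms can have equal means and fail that null, or have very different means and satisfy it.

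Many small pad and consultation costs combined with a few operations or admissions give a long right tail, so Shapiro-Wilk will very probably reject and the fallback will be used. One secondary outcome then carries two between-group results that can disagree, and the protocol gives no rule for which of them supports a statement that one treatment costs more.

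**Working it through.** **Inputs.** From the protocol: significance level 5% (two-sided assumed); 44 women per group, made up of 40 plus 4 for loss; Shapiro-Wilk as the trigger. The protocol states no figure for the cost test and no cost distribution, so there is nothing of its own to reproduce and every shape below is an assumption. The fallback is taken to be a rank test. Each woman contributes one total cost, a simplification of the planned group-by-stage analysis.

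**1. Is the switch the expected path?** In every skewed scenario simulated, at 40 and at 44 per arm, Shapiro-Wilk on the residuals rejected in 100% of trials.

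**2. Equal means, unequal shapes, two arms of 40.** For lognormal costs with coefficient of variation CV, the log-variance is s² = ln(1 + CV²). With equal arithmetic means the log-means differ by d = (s₂² − s₁²)/2. The probability that a cost from the less variable arm exceeds one from the other is θ = Φ(d/√(s₁² + s₂²)). The Mann-Whitney standard error under the null is √((2n+1)/(12n²)) = √(81/19200) = 0.0650. Approximate rejection is Φ(z − 1.96) + Φ(−z − 1.96), with z = (θ − 0.5)/0.0650.

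| CV pair | s₁², s₂² | d | θ | z | Rejection, formula | Rejection, simulation |
|---|---|---|---|---|---|---|
| 1 and 1 | 0.693, 0.693 | 0 | 0.500 | 0 | 5% | about 5% |
| 0.5 and 1 | 0.223, 0.693 | 0.235 | 0.597 | 1.49 | 32% | 34% |
| 1 and 2 | 0.693, 1.609 | 0.458 | 0.619 | 1.83 | 45% | 44% |
| 0.5 and 1.5 | 0.223, 1.179 | 0.478 | 0.657 | 2.41 | 67% | 69% |
| 0.5 and 2 | 0.223, 1.609 | 0.693 | 0.696 | 3.01 | 85% | 87% |

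Formula and simulation (2000 trials each) agree. The first row shows that skew alone does no harm.

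**3. Equal means with a fixed fee in one arm.** With the fee making up 25%, 50% or 75% of that arm's mean cost, the simulated rank test rejects in 15%, 41% and 61%. With a 10% share it stays near nominal.

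**4. Three arms, equal means, Kruskal-Wallis, 44 per arm.** Log-SDs of 0.5/0.75/1.0 give 49%, 0.5/0.5/1.0 give 57%, 0.8/1.0/1.2 give 33% and 0.5/1.0/1.5 give 97%. Identical arms give 5%. One-way ANOVA on the four unequal-shape sets rejects in 8%, 8%, 6% and 13%. At 40 per arm the Kruskal-Wallis figures are 44%, 53%, 32% and 95%.

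**5. The reverse error.** Suppose a fraction p of one arm has a procedure costing more than nearly all other women's costs, and the arms are otherwise alike. Then θ = 0.5 + p/2.

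- p = 10%: θ = 0.55, z = 0.77, power 12%.
- p = 20%: θ = 0.60, z = 1.54, power 34%.

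Simulation with that arm's mean doubled gives the same 12% and 34%, against 76% and 95% for the bootstrap. A further set of runs with other assumed distributions gave 10% to 33% against 63% to 82%. With equal medians of 200 and means of 227, 265 and 330, Kruskal-Wallis rejects in 5%, and the bootstrap interval for the outer pair excludes zero in 46%.

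**6. How good is the alternative?** Under equal means the bias-corrected bootstrap (two arms of 40) excluded zero in 7% to 12% of trials. A percentile bootstrap gave 7% to 14% at 44 per arm and 9% to 16% at 40. That is liberal, but much less sensitive to shape than the rank test.

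**The case against.** A reader might infer that the rank test displaces the mean comparison, so that the economic aim itself is answered by ranks. The documents do not support this. The cost-utility item stands on its own, is tied by its wording to comparing costs between groups, and supplies the cost-effectiveness and cost-utility ratios and the acceptability curves. None of these uses the ANOVA rule or its fallback, and nothing overrides the bootstrap.

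Four further objections have force.

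- The fallback is called only non-parametric, and a permutation test of means would also qualify. A rank test is the usual reading, not the stated one.
- Excess rejection requires shapes that differ by arm. Ten supervised sessions in two arms against a booklet in the third make that plausible, but the protocol does not say that intervention fees and NMES materials enter the cost form. Evaluation tools lists the materials as part of the economic evaluation, and the sessions end before follow-up. The fixed-fee scenarios may therefore not apply to this variable.
- Exactly equal means with very different shapes is a narrow case, and the largest percentages need CVs three- to fourfold apart.
- The simulations use one total per woman, not repeated measurements.

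These points limit the size of the problem. They do not remove it: the same outcome is still compared in two ways that answer different questions, and the rule as written still sends skewed costs to a test that is not about mean cost. Naming the fallback may properly be left to a fuller document; the conflict between the two items stands in this one.

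**Conclusion.** The point holds as a conflict between two cost comparisons with no precedence, and it should be corrected. Non-normality is very likely enough for the switch to be treated as the default. If the fallback is a rank test and cost shapes differ between arms, equal-mean arms would be declared different in roughly 15% to 87% of two-arm comparisons, and in up to 97% in the most extreme three-arm case. With identical shapes the rate is about 5%. A doubling of mean cost caused by procedures in 10% to 20% of one arm would be detected by ranks in only about 10% to 34% of trials. All these figures rest on assumed distributions.

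The damage is confined to the reported significance of a secondary outcome and to a possible contradiction with the bootstrap in the same report. It would be wrong to conclude that the economic evaluation is invalid, or that skew by itself inflates the error rate.

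**What to change.** In the end-of-treatment and end-of-follow-up items of the Statistical analysis plan, remove the health cost form from the ANOVA/non-parametric rule. Alternatively, keep it there and label that analysis descriptive, which preserves the view of costs by stage. In the cost-utility item, name the baseline-corrected difference in arithmetic mean cost, with the planned 5000-replicate bias-corrected bootstrap 95% interval, as the only inferential cost comparison, for IG1 versus CG, IG2 versus CG and IG2 versus IG1. Medians and ranges remain as description.

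The cost is a wording change, with no new data or method. The report should state that the bootstrap interval is somewhat liberal at about 40 women per arm with heavy skew: about 7% to 14% rejection under equal means in most of the runs above, and 16% in the worst.

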## Methods

### Trial design

This is study is a randomized controlled trial with a blind assessor and economic evaluation. Outcome measures will be assessed at baseline (before treatment begins), on the last day of treatment (after the 10th session), and up to 6 months after the treatment is completed (follow-up). From January 2022, participants will be invited and randomized into three groups by a simple randomization using an electronic system “Randomization Main” and a ratio of 1:1:1. The data for the primary outcome will be collected until the end of 2023 and the follow-up data until the first semester of 2024. This project will follow the guidelines of the *Consolidated Standards of Reporting Trials* (CONSORT) and *Standard Protocol items: recommendations for interventional trials* (SPIRIT) [15] items.

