To assess the presence of urinary symptoms, participants will be instructed to complete a 24-h voiding diary. This instrument contains questions related to the urinary habits, such as the information on number of urinations, amount of urine eliminated, and occurrence of urinary loss. In addition, the voiding diary will quantify the use of absorbents, diapers, and linings (if used and the number of changes) [24, 25]. Participants will be encouraged to complete the voiding urinary twice: once at the pre-treatment before the beginning of the intervention and at the end of the treatment (10th session). The results from the voiding diary will be analyzed by urine loss frequency, considering the urinary leakage associated to stress (e.g., coughing, sneezing, physical exercise or household activities).

Health costs related to UI will be assess by two different questionnaires: (i) SF-6D, validated to Brazilian Portuguese by Campolina et al. [26], and (ii) *King´s Health Questionnaire for Scoring Algorithm*, elaborated by Brazier et al. [27]. The SF-6D evaluates items related to functional capacity, global limitation, physical aspects, emotional aspects, social aspects, pain, mental health, and vitality. This questionnaire allows to generate utility indexes (adjusted by years of life) from data of effectiveness used in economic analyzes. The *King´s Health Questionnaire for Scoring Algorithm* is based on specific health measures of UI, which assesses utility based on quality of life with a five-dimensional classification: functional limitation, physical limitation, social limitation, emotions, and sleep. This questionnaire presents a score of validity pointed in 0.62. Both questionnaires have a unique score ranging from 0 to 1 (where 0 represents the worst health status and 1 represents the better health status) [27].

The psychometric properties of the instruments and procedures are present in Table 2.

**Table 2 Tab2:** Psychometric properties of the instruments and procedures

Examination procedure	Description of procedure	Indicator of musculoskeletal dysfunction	Reported psychometric properties
Modified Oxford Scale (MOS)	Vaginal palpation performed by introduce of two fingers inside participant vaginal canal	Subjective evaluation of PFM function	Intra-rater reliability of MOS (Kappa test) [19] Bidigital palpation 0.75 Inter-rater reliability of MOS (Kappa test) Bidigital palpation 0.60

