Manometry	Peritron^TM^ manometer: insertion of a probe into the vaginal canal of participant	Objective evaluation of PFM function	Intra-rater reliability 0.96 [28]
KHQ	Score variating 0 to 100 = the higher the score, the worse the quality of life	Impact of urinary loss	Internal consistency 0.87 [17] Reproducibility: evaluated by Pearson’s coefficient for all domains [29] (listed below): Perception of health 0.36 Impact of incontinence 0.60 Limitations of daily activities 0.75 Physical limitation 0.74 Social limitation personal relationship 0.82 Emotions 0.76 Sleep/energy 0.62 Severity measures 0.71 Minimum relevant clinical difference: 5 points [23] Responsiveness: evaluated by Cronbach’s alpha for all domains [30] (listed below): General health perception − 0.76 Impact of incontinence − 1.94 Role limitations − 1.50 Physical limitations − 1.49 Social limitations − 1.33 Personal relationships − 0.76 Emotions − 1.44 Sleep/energy − 0.86 Severity measures − 2.40
SF-6D	Score between 0 to 100 = the higher the score, the better the health status	Quality of life that constructed data about effectiveness, used in economic analyzes	Internal consistency: – Reproducibility intra-rater: evaluated by Pearson’s correlation coefficient for all domains [31] (listed below): Functional capacity 0.8 Physical aspects 0.63 Social aspects 0.75 Emotional aspects 0.44 Pain 0.54 Vitality 0.65 Mental health 0.69 General health status 0.84 Specificity: – Minimum relevant clinical difference: – Responsiveness: 0.404 (performed in women with postoperative pelvic organ prolapse; the value of the total score was used to identify the result of responsiveness through the ANOVA test) [32]
King’s Health Questionnaire for Scoring Algorithm	Score: 0 = worst health status 1 = better health status	Health measures of UI	Internal consistency: – Reproducibility: – Specificity: – Minimizes relevant click difference: – Responsiveness: evaluated by standardized response mean (SRM) for all domains (listed below). The SRM is a version of the effect size that divides the mean change by the standard deviation of the change [27]: Role 0.56 Physical 0.51 Social 0.39 Personal 0.33 Emotions 0.37 Sleep 0.41 Severity 0.50 Valid: –

MOS, Modified Oxford Scale; PFM, pelvic floor muscle; KHQ, King’s Health Questionnaire; SF-6D, Short-Form 6 Dimensions—Brazil; UI, urinary incontinence

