### Interventions

Ten treatment sessions will be held, once a week, with a total of 10 weeks of attendance. The participants will be instructed to perform the protocol daily at home. The CG (control group) will receive an orientation booklet for the proposed protocol. The IG1 will perform PFM protocol with physiotherapist supervision 1 time a week and will be instructed to perform the exercise at home without supervision, and the IG2 will perform the PFM protocol (only in supine/lying position) associated with the intravaginal NMES technique with a physiotherapist supervision for 20 min, once a week.

PFM will be performed as the protocol proposed by Bø, Talseth e Holme [33]:
Positions: lying, kneeling, sitting, and standing;Series: 1 series of exercise for each position;Repetitions: 12 sustained contractions with 6 s of duration;Rest: 6 s;After repetitions of sustained contractions, 4 fast contractions are added;Intensity: maximal voluntary contraction;Session duration: 45 min.

The intravaginal NMES technique, applied to IG2, will be performed with the Dualpex 961 equipment (Quark Medical Products), following the description of the parameters suggested by the study conducted by Barbosa et al. [34]. The participants will remain in supine position, with flexion of the hips and knees. The physiotherapist responsible for the interventions will wear procedure gloves during the entire session and will apply lubricating gel on of the vaginal probe that will be introduced into the participant’s vaginal canal. During the period of NMES application, the physiotherapist will fix the probe manually. At the end of study, vaginal probes will be discarded. The parameters used during NMES application are described in Table 3. In the first 5 treatment sessions, the ON time stimulus will be fixed in 5 s, and the OFF time stimulus will be 15 s. For the last five treatment sessions, the OFF time stimulus will be decreased to 10 s.

**Table 3 Tab3:** Randomized controlled blinded ES parameters

	1–5th session	6–10th session
Phase duration (μs)	700	700
Frequency (Hz)	50	50
Ramp-up (s)	1	1
Stimulus on time (s)	5	5
Ramp-down (s)	0	0
Stimulus off time (s)	15	10
Duty-cycle ratio	1:3	1:2
Time (min)	20	20

μs, microseconds; Hz, Hertz; s, seconds

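### The QALY is defined as a 0–1 utility index, although at most about 0.69 QALYs can accrue in this trial, and the utility scales behind it are described inconsistently

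*Protocol article*

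**What the plan says.** The cost-utility item in the Statistical analysis plan states that the QALY "combines the length and quality of life into a single index number between 0 and 1". It then anchors both ends of that index to states of health: "where 0 corresponds to a health state judged to be equivalent to death and 1 corresponds to optimal health".

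The utilities come from two instruments, the SF-6D and the King's Health Questionnaire scoring algorithm. Evaluation tools says that both give one score from 0 to 1, "where 0 represents the worst health status and 1 represents the better health status". Table 2 in the same section gives the SF-6D a different range: "Score between 0 to 100 = the higher the score, the better the health status". On the SF-6D, Evaluation tools adds: "This questionnaire allows to generate utility indexes (adjusted by years of life) from data of effectiveness used in economic analyzes".

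On timing, Interventions says: "Ten treatment sessions will be held, once a week, with a total of 10 weeks of attendance". Trial design adds follow-up to 6 months after treatment. Both instruments are completed at baseline and at the end of treatment, and then "at the 3rd and 6th month of follow-up, the SF6-D, KHQ, King´s Health Questionnaire for Scoring Algorithm, and health cost analysis form will be completed". The section on primary and secondary outcomes places the economic evaluation in the 6 months of follow-up, whereas the Statistical analysis plan also applies the cost form at baseline and at the end of treatment.

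**The concern.** An index equal to 1 in optimal health, however long that health lasts, contains no time. It is the weight from which QALYs are built. Over exactly one year the two would coincide at the top of the scale, but this trial does not last a year.

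The zero point matters as well. A QALY calculation needs weights on which death is zero. If the scores that feed it have zero at worst health, a given change in health is a different number of units on each scale. The text does not tell an analyst which scale applies, and the 0 to 100 range in Table 2 adds a third description.

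Cost-utility is part of the stated secondary aim, and the Introduction presents such analyses as input to public funding decisions. In a valid cost-utility ratio the QALY difference is the denominator, so an error in its scale passes straight into cost per QALY.

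**Working it through.** The article gives no QALY total, no horizon in years and no cost per QALY, so there is no figure to reproduce. The check asks what the stated definition would imply.

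**Inputs.** Treatment of 10 weeks (Interventions); follow-up of 6 months (Trial design); utilities at baseline, week 10, and months 3 and 6 of follow-up (Statistical analysis plan). The utility differences below are assumed for illustration.

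**1. Largest possible QALY total.** Horizon H = 70/365.25 + 0.5 = 0.192 + 0.5 = 0.692 years. Optimal health throughout gives 1 × 0.692 = 0.69 QALYs, whereas the stated definition assigns 1. If the economic horizon is only the follow-up period, the maximum is 0.5.

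**2. Time-averaged index used as the QALY.** The true QALY difference equals the average utility difference × H. Leaving out H overstates the gain by 1/0.692 = 1.45. Cost per QALY is then 0.692 of its correct value, which is 1 − 0.692 = 31% too low. This holds for any effect profile over the 0.69-year horizon.

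**3. Index at a single visit used as the QALY.** The true QALY difference is the trapezoid area under the between-group utility difference. Cost per QALY relative to its correct value is that area divided by the index difference used.

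| Assumed difference at baseline, week 10, month 3, month 6 | Area | Week-10 index used | Month-6 index used |
|---|---|---|---|
| 0, 0.05, 0.05, 0.05 | 0.0298 | 0.60 (40% too low) | 0.60 (40% too low) |
| 0, 0.05, 0.035, 0.02 | 0.0223 | 0.45 (55% too low) | 1.11 (11% too high) |
| 0, 0.02, 0.035, 0.05 | 0.0194 | 0.97 (3% too low) | 0.39 (61% too low) |

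First row: 0.05 × (0.192/2 + 0.5) = 0.0298, and 0.0298/0.05 = 0.596.

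**4. Where the direction turns.** Let the difference rise linearly to week 10 and then fall linearly to a fraction r of its week-10 value at month 6. The month-6 index gives the correct answer when 0.096 + 0.25 × (1 + r) = r, so r = 0.346/0.75 = 0.46. Below that fraction, cost per QALY is too high.

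**5. Zero point.** If worst health has utility w on a death = 0 scale, an index with worst health at zero multiplies every difference by 1/(1 − w). Differences are stretched if w is positive and shrunk if worst health is rated below death. The documents give no w, so neither the size nor the sign can be stated.

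**The case against.** The best defence is that this is a loose textbook gloss and not a calculation rule. The sentence does mention length of life, and the description of the SF-6D mentions years of life. No section says that an index difference will enter without a time weight. A total between 0 and 0.69 also lies between 0 and 1. Computing an area under the curve is detail that a journal article commonly leaves to the full protocol or analysis plan. All of this stands, and the absence of a trapezoid rule is not the point raised here. It does not rescue the definition, because assigning 1 to optimal health is wrong for a horizon of 0.69 years, whatever detail is held elsewhere.

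A reader might go further and infer that the planned analysis will understate cost per QALY and so favour the supervised arms. The article does not support that. As written, its incremental ratio divides total costs by cost differences, so no QALY appears in it at all. That is a separate error, but it means that no biased cost per QALY follows directly from the text. The direction can also reverse, as steps 4 and 5 show, and the article contains no results on which arm costs more or gains more.

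On the zero point, the Evaluation tools wording may only name the two ends of a score that is in fact anchored at death. The conflict would then be a slip of wording with no numerical effect. The article does not settle this, and no section says that scores will be rescaled.

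The horizon is also less settled than 0.69 suggests, since one section ties the economic evaluation to the 6 months of follow-up.

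**Conclusion.** The point holds as an error of definition together with an internal contradiction. What is called a QALY is a utility weight, and the most that can accrue is about 0.69 from baseline, or 0.5 if the economic horizon is follow-up alone. Zero is death in the Statistical analysis plan and worst health in Evaluation tools, and the SF-6D has two ranges.

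The numerical consequence is conditional. If a time-averaged index difference over the 0.69 years were used with no time weight, the gain would be overstated 1.45-fold and cost per QALY would be about 31% too low. Other choices of index or effect profile give other sizes and can give the opposite sign. No figure can be attached to the conflict over zero. These numbers show what is at stake if the definition is taken literally. They are not a predicted bias of the trial.

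It should be corrected before analysis, because cost-utility is a stated secondary aim and nothing else in the economic text supplies the right definition.

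**What to change.** In the cost-utility item of the Statistical analysis plan:

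- State that utilities lie on a scale from 0 (death) to 1 (full health), after checking this against the scoring rules of both instruments.
- Define QALYs as the area under each woman's utility curve, by the trapezoid rule over baseline, week 10, and months 3 and 6 of follow-up, with a maximum of about 0.69.
- State the economic horizon once and use it for both costs and QALYs. If only follow-up is meant, the curve starts at week 10 and the maximum is 0.5.
- Put the between-group QALY difference in the denominator of the cost-utility ratio and the cost difference in the numerator.

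In Evaluation tools, including Table 2, bring the score ranges and zero points of the SF-6D and the King's scoring algorithm into line with each other and with the item above.

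The cost is a few sentences. The utility measurements are already scheduled, so no visits, data or participants are added. The drawback is that cost per QALY may look less favourable than it would with an untimed index.
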